## Abstract

**Background:**

Red blood cell (RBC) transfusion is frequently employed in both ambulatory and hospital environments with the aim of improving patient functional status. In the ambulatory setting, this practice is particularly common in patients with malignancy due to anemia associated with their cancer therapy. Increasingly, the efficacy of this US$10.5 billion per year practice has been called into question. While it is often standard of care for patients with chemotherapy-induced anemia to receive ambulatory RBC transfusions, it is unclear to what extent such transfusions affect home functional status. It is also unclear whether or not changes in functional status in this population can be objectively quantified using wearable activity monitors. We propose to directly measure the impact of outpatient RBC transfusions on at-home functional status by recording several physiological parameters and quantifiable physical activity metrics, e.g., daily energy expenditure and daily total step count, using the ActiGraph wGT3X-BT. This device is an accelerometer-based wearable activity monitor similar in size to a small watch and is worn at the waist. Study participants will wear the device during the course of their daily activities giving us quantifiable insight into activity levels in the home environment.

**Methods/design:**

This will be a randomized crossover pilot clinical trial with a participant study duration of 28 days. The crossover nature allows each patient to serve as their own control. Briefly, patients presenting at a tertiary medical center’s Ambulatory Infusion Center (AIC) will be randomized to either: (1) receive an RBC transfusion as scheduled (transfusion) or (2) abstain from the scheduled transfusion (no transfusion). After an appropriate washout period, participants will crossover from the transfusion arm to the no-transfusion arm or vice versa. Activity levels will be recorded continuously throughout the study using an accelerometry monitor. In addition to device data, functional status and health outcomes will be collected via a weekly telephone interview. The primary outcome measure will be daily energy expenditure. Performance metrics, such as step count changes, will also be evaluated. Additional secondary outcome measures will include daily sedentary time and Patient-reported Outcomes Measurement Information System (PROMIS) Global 10 Survey scores.

**Discussion:**

This trial will provide important information on the feasibility and utility of using accelerometry monitors to directly assess the impact of RBC transfusion on patients’ functional status. The results of the study will inform the merit and methods of a more definitive future trial evaluating the impact of ambulatory RBC transfusions in the target population.

**Trial registration:**

ClinicalTrials.gov, identifier: NCT02835937. Registered on 15 July 2016.

**Electronic supplementary material:**

The online version of this article (doi:10.1186/s13063-017-1873-z) contains supplementary material, which is available to authorized users.

## Background

The number of red blood cell (RBC) units transfused annually approaches 14 million in the United States (US) alone [1]. With an estimated cost of US$761 per RBC unit [2], this equates to US$10.5 billion in annual health care expenditures. Notably, the efficacy of RBC transfusion has been increasingly called into question [3]. This fact, when considered in concert with the underappreciated costs and risks of RBC transfusion, has resulted in a progressive move towards more conservative RBC transfusion practices [4].

Importantly, the evidence underlying these trends has primarily focused on the provision of RBC transfusion in the hospital environment. In contrast, very little data are available to guide transfusion practices in the outpatient ambulatory setting. This represents a key knowledge gap in current transfusion practice, and addressing this gap is an important goal of the proposed study.

In the ambulatory environment, RBC transfusions are frequently administered with the intention of improving patients’ functional status. Indeed, survey responses suggest that a patient’s functional status is the second leading indication for RBC transfusion trailing only the pretransfusion hemoglobin (Hgb) value [5]. However, data supporting this practice are extremely limited. A secondary outcome of the well-publicized Transfusion Trigger Trial for Functional Outcomes in Cardiovascular Patients Undergoing Surgical Hip Fracture Repair (FOCUS) specifically evaluated the impact of RBC transfusion practices on gross measures of patient’s functional status [6]. In this large clinical trial, more liberal RBC transfusion practices were not associated with improved functional status. Additional investigations have also failed to identify an association between the presence of anemia and quality of life (QoL) measures [7].

In contrast, a limited number of investigations do in fact support improved functional status with more liberal RBC transfusion practices [3, 8]. These investigations typically evaluate patient functional status in the health care environment (e.g., Timed Up and Go Test in the health care provider’s office [9]) or via survey responses to questionnaires such as the Medical Outcomes Study 36-Item Short-Form Health Survey (SF-36) [8].

Importantly, no well-designed trials have evaluated the impact of RBC transfusion on functional status in the patient’s home environment, arguably a far more relevant outcome to potential transfusion recipients. Indeed, the efficacy of RBC transfusion in the ambulatory setting remains very much a matter of debate. To this point, ongoing equipoise in this area was recently highlighted at the 2015 National Heart, Lung, and Blood Institute State of the Science Meeting in Transfusion Medicine where the identification of new strategies or technologies that may help to clarify the role of RBC transfusion in the ambulatory setting was noted to be a topic of significant interest.

Beyond unclear efficacy in the ambulatory setting, it is also important to recognize that every transfusion episode carries the potential for meaningful risk. As examples, transfusion-related acute lung injury (TRALI) and transfusion-associated circulatory overload (TACO) are respiratory complications resulting from transfusion and are the leading causes of transfusion-related death in the US [10]. Although great strides have recently been made in predicting patient-specific risk prior to transfusion [11–13], the risk remains serious. Furthermore, despite their significance, patients and their clinical teams frequently fail to recognize these transfusion-related respiratory complications [14–16]. Compounding the risk landscape is the consideration that at present there are essentially no data evaluating the risks of transfusion in the ambulatory setting.

The introduction of innovative mobile health (mHealth) technologies creates unique opportunities to study patients’ functional status in a more robust manner and in the setting that matters most: their home. Indeed, as the accuracy of these novel devices improves, their potential application to studying outcomes in the home environment moves closer and closer to a reality.

### Aims and objectives

#### Primary

In light of the ongoing equipoise regarding the efficacy of RBC transfusion in the ambulatory setting, the known risks associated with blood product administration, and the availability of innovative technologies that are able help to address these concerns, the primary aims of our proposed protocol are as follows:
**Specific aim 1**: to evaluate the impact of RBC transfusion on home functional status as assessed by physical activity metrics recorded by a wearable ActiGraph wGT3X-BT mHealth device. We hypothesize that the percent change in mean daily physical activity in the 7 days following randomization will be greater during the study periods where participants received an RBC transfusion than during the periods where an RBC transfusion was not received.
**Specific aim 2**: to evaluate the correlation between physical activity as assessed by the accelerometer and subjective functional status as assessed with the Patient-reported Outcomes Measurement Information System (PROMIS) Global 10 Survey. We hypothesize that there will be a direct correlation between physical activity as assessed by the device and the subjective functional status as assessed by the PROMIS Global 10 Survey.

### Secondary

As a pilot trial we further delineate a set of secondary objectives. These are less formal than our primary objectives and are designed to gauge study feasibility, with a particular focus on scalability of methods to a potentially larger future trial. To that end we aim to evaluate the suitability of the ActiGraph wGT3X-BT for use in our target population. While the device has been validated in terms of its technical measurement [17–22], it remains an open question as to whether or not our patient population, most of whom are receiving chemotherapy or are transplant recipients, will display a level of adherence that is sufficient for answering our larger clinical question. We will also monitor enrollment volume, trial completion volume, device failure rates, and other such measures which might be of practical importance when considering scaling to a larger future trial.

In order to consider whether or not to move forward from a pilot trial to a larger future randomized clinical trial, we will carefully evaluate the results for a signal of efficacy. If there is strong evidence that RBC transfusion is efficacious in improving patient activity levels a larger trial is less likely to be considered. Alternatively, if there is evidence that “no transfusion” is better, or if the results are equivocal, we are more likely to pursue a larger trial. In addition to intervention efficacy, we will also assess both the feasibility of scaling the trial to a more definitive phase II/III design and the impact of any adverse events. We will carefully consider participant adherence rate and the potential for increasing enrollment as prerequisites for proceeding to a larger trial. Adverse events, if any, will be evaluated as outlined by the Safety and Monitoring Plan (Additional file 1). The final document reporting the results of this trial will follow the main Consolidated Standards of Reporting Trials (CONSORT) 2010 Statement: extension to randomized pilot and feasibility trials [23]. Both this trial and any future trial will follow the Standard Protocol Items: Recommendations for Interventional Trials (SPIRIT) Checklist (Additional file 2).

## Methods/design

### Study design

This will be a randomized, two-group, crossover, pilot clinical trial (Fig. 1). Following this design each subject serves as their own control. Randomization is to help eliminate bias due to any time-dependent change in subject health or chronological effects that may result from a nontransfusion period.

**Fig. 1 Fig1:**
[figure not shown]
Study design

### Participants and screening

Study participants will be identified in the Ambulatory Infusion Center (AIC) of a tertiary care medical center. The study population will consist of adult (aged 18 years or older) male and female hematology and oncology patients presenting to the AIC with anemia (Hgb under practice standard threshold for transfusion, e.g., 7.0–9.0 g/dL) and who are planned to undergo routine RBC transfusion. Subjects with at least one prior presentation to the AIC within 3 months of the screening visit will be eligible for study participation. This inclusion criterion has been selected due to the fact that our preliminary research indicates that those who present to the AIC on more than one occasion for RBC transfusion are highly likely to present for a subsequent RBC transfusion in a 28-day time frame. A full list of the inclusion and exclusion criteria are provided in Table 1.

**Table 1 Tab1:** Inclusion and exclusion criteria

Inclusion criteria	Exclusion criteria
Age ≥18 years	Refusal to provide informed consent
At least one prior encounter in the AIC	Refusal by the health care team
Planned RBC transfusion	Acute ischemia (e.g., myocardial infarction (MI), cerebrovascular accident (CVA))
	Hgb <7.0 g/dL
	Active bleeding
	Symptomatic anemia (hypotension, tachycardia, angina, syncope/presyncope believed related to anemia)
	Nonambulatory functional status
	Established or uncertain pregnancy status

*AIC* Ambulatory Infusion Center, *RBC* red blood cell

For the exclusion criteria of pregnancy, potential study participants in the reproductive age group will be asked if they might be pregnant. If the response is “yes” or “unknown,” the potential study participant will be excluded. Screening/consent logs will be maintained centrally to allow generation of a CONSORT diagram, but will also made available to the transfusion medicine service at Mayo Clinic in Phoenix, AZ, USA to facilitate the procedures outlined below. Consenting participants will be provided with an accelerometer to wear continuously for the duration of their involvement in the trial (28 days). This device, described further below, will automatically capture relevant physiological data with no need for intervention by the patient. Following the trial, participants return the device by mail and data are retrieved by the investigative team.

The accelerometer chosen for this study is the ActiGraph wGT3X-BT (ActiGraph Corp, Pensacola, FL, USA). These devices are similar in size and weight to a simple wristwatch, and are typically worn at the wrist, ankle or waist. By capturing and interpreting acceleration data the device objectively measures a patient’s physical activity through metrics such as step counts, energy expenditure, daily metabolic equivalent (MET) rates, activity intensity, activity bouts, and sedentary bouts. For the current study, the devices will be worn at the waist in consideration of the more extensive peer review given to waist-based algorithms used to interpret raw accelerometer data. Additional measurable quantities include wear time, heart rate, RR intervals, and body position.

All study participants will be contacted weekly via telephone for the duration of the study (expected to be 28 days). The purpose of these communications is to better understand wearability, enhance protocol compliance, and assess satisfaction with the device. The Data Capture Form used by the study coordinator (SC) is available as supplemental material to this article (Additional file 3). All comments by participants will be logged by the SC, giving the team insight into participant interaction with the device and protocol. Inquiries into life events that may impact home functional status (e.g., injuries, illnesses, other events) will also be made. Finally, symptoms related to the intervention of interest (transfusion versus no transfusion) will also be assessed during each of these correspondences. Specific inquires will include evidence of profound anemia, renal failure, myocardial infarction, nonhemorrhagic stroke, mesenteric ischemia, syncope, falls, shortness of breath, and chest pain or pressure as well as any medical encounters including nonstudy transfusion events. All responses will be augmented with data recorded in participants’ electronic health records.

### Randomization

After informed consent has been obtained, study participants will be stratified into those that are actively receiving chemotherapy and those that are not. Within each stratum, participants will be randomized using simple randomization (Pr(transfusion group first) = 0.5). Patients successfully enrolled will be randomized to one of two transfusion/no transfusion sequences (Fig. 1). The SC will obtain the randomized sequence from the Research Electronic and Data Capture (REDCap) randomization module. After randomization, the SC will inform the AIC of the appropriate timing of the no-transfusion study period so that an updated order set can be prepared. It is recognized that using simple randomization may result in imbalances in the transfusion sequences, but simple randomization was selected for this study for ease of implementation. The crossover design also helps mitigate confounding provided that there is no period effect observed in the data.

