### Primary analysis

The primary outcome analyses will be performed using an “as treated” rather than an “intention-to-treat” analysis set while accounting for the crossover design. This approach is most appropriate for this pilot clinical trial, which primarily aims to understand home functional status as it relates to ambulatory RBC transfusion. For statistical comparisons, we will fit a random effects model that utilizes daily total energy expenditure as the dependent variable and days from transfusion or control visit (“placebo” visit where no transfusion was performed). For simplicity, we will include the mean daily measurements for the 3 days prior to the transfusion/control visit as covariates in the model, and consider the 7 days after transfusion/control visit in the model. This censoring of data beyond 7 days after the transfusion/control visit is to avoid carryover effects with the model. We will test the transfusion indicator by study day interaction, with adjustment for baseline activity, for the primary hypothesis. This parameter will quantify how the profile of activity differs with and without transfusion while accounting for the variation in activity between participants by means of the random effect and baseline adjustment. Contrasts will be constructed to quantify the difference in the change in activity between these visits.

Sensitivity analyses will attempt to model the change in activity levels in the days after transfusion. These exploratory models will consider a potential initial boost in activity with linear or exponential trends to account for the change in activity over the 7 days after transfusion. These models will also include subject random effect and account for time-series correlation. These analyses will be expanded to include all data measured over the 28-day period.

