### Sample size considerations and recruitment

This is a pilot study to determine whether accelerometers are sensitive enough to detect change in functional status in patients undergoing ambulatory transfusion services. The primary hypothesis is to detect change in total energy expenditure after the transfusion in both between and within individual comparisons. A minimum clinically relevant difference is not yet known for this outcome. To estimate the sample size, we approach the calculation from the perspective of having sufficient data to estimate the standard deviation so that we could plan a follow-up study. Julious [27] recommends studying 12 participants per group for such aims. We apply this recommendation to this study by assuming that we want at least 12 participants to complete the first randomized phase of the crossover design (i.e., the parallel group portion of the study). Based on this, we will want to have at least 24 subjects who will provide evaluable data from the activity monitor. We therefore adjust the sample size upwards by 25% to account for attrition and/or changes in the transfusion schedule. Thus, our total planned sample size is 30 participants. Preliminary research with clinicians familiar with the infusion center patient population suggests that an enrollment of this size should be readily achievable. Specific strategies for achieving adequate enrollment include presentations to the hematology and oncology practices in order to advertise the study to providers, as well as access to the Mayo Clinic patient scheduling and electronic health record system. This will ensure the ability to have sufficient on-site recruiting staff on days where patients known to be eligible are scheduled for transfusion.

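### With sequences that may be unequal, the protocol relies on no period effect being observed; the primary model should carry a prespecified period term instead

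*Protocol article*

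**What the plan says.** The Study design section gives randomization the task of protecting against change over time: "Randomization is to help eliminate bias due to any time-dependent change in subject health". The Randomization section first separates patients by treatment status ("study participants will be stratified into those that are actively receiving chemotherapy and those that are not") and then allocates without restriction inside each stratum ("participants will be randomized using simple randomization (Pr(transfusion group first) = 0.5"). It discloses the consequence, "It is recognized that using simple randomization may result in imbalances in the transfusion sequences", justifies the choice by ease of implementation, and adds the condition at issue: "The crossover design also helps mitigate confounding provided that there is no period effect observed in the data".

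The Primary analysis section describes a random effects model for daily energy expenditure. The terms it names are day from the visit, the mean of the 3 days before that visit, the transfusion-by-day interaction (the primary test) and a subject random effect. It describes the model as "accounting for the variation in activity between participants by means of the random effect and baseline adjustment" and also promises contrasts for the difference in change between the two kinds of visit. It says in general terms that the crossover is accounted for, but names no period or sequence term and no check for a period effect.

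The sample size section cites a source that "recommends studying 12 participants per group for such aims", applies this to the first, parallel-group phase, and arrives at 24 evaluable and 30 enrolled.

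**The concern.** In a two-period crossover, equal sequences cancel a period shift out of the within-person treatment contrast. With unequal sequences, a period term in the model does that job. This protocol gives up the first safeguard and does not name the second. In their place it puts a condition on the data, that no period effect be observed, which a trial of this size is poorly able to test. The Study design section itself treats time-dependent change in health as a real possibility.

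What is at stake is the estimate for the split actually obtained. If that split is uneven and activity drifts between the first and second visit, part of the drift is reported as a transfusion effect, or is taken away from one. The protocol intends to use the efficacy signal in deciding whether to run a larger trial, so this matters even in a pilot.

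Two smaller matters belong to the same passage. Stratifying by chemotherapy suggests a balance that simple randomization does not give. And 12 per group in the first phase is not something this allocation secures.

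**Working it through.** **Inputs from the protocol.** Allocation probability 0.5, unrestricted within strata (Randomization). 12 per group, 24 evaluable, 25% inflation, 30 enrolled (Sample size considerations and recruitment). Model terms as listed under Primary analysis. The protocol gives no SD, retention rate by sequence or size of period shift; the values used for these below are assumptions.

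**The plan's own figure.** 2 × 12 = 24, and 24 × 1.25 = 30. This reproduces.

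**Sequence split**, exact Binomial(n, 0.5):

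| Event | Probability |
|---|---|
| 24 evaluable, exactly 12:12 = C(24,12)/2^24 | 16.1% |
| 24 evaluable, 15:9 or more uneven | 30.7% |
| 24 evaluable, 16:8 or more uneven | 15.2% |
| 30 randomized, no loss, at least 12 in each sequence | 80.0% |

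**Stratification.** The sum of independent Binomial(s, 0.5) and Binomial(30 − s, 0.5) counts is Binomial(30, 0.5) for any s. Simulated strata of 15/15, 20/10 and 24/6 all gave about 80% for at least 12 in each sequence, as with no strata.

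**How a period shift enters.** Let τ be the transfusion effect and π the second-minus-first period shift left after baseline adjustment. The transfusion-minus-control difference has expectation τ − π in those transfused first and τ + π in those transfused second. With no period term, given the split:

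E(estimate) = τ + π × (n2 − n1)/N,

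where n1 were transfused first and n2 second. The fraction of π that enters, in absolute value, is:
- 12:12: 0
- 13:11: 2/24 = 8%
- 14:10: 4/24 = 17%
- 15:9: 6/24 = 25%
- 16:8: 8/24 = 33%

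**Can the stated condition be checked?** In units of the SD of the paired difference, the estimated π has standard error 0.5 × √(1/n1 + 1/n2), which is 0.204 at 12:12 and 0.217 at 16:8. Power of the two-sided 5% t test with 22 df:

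| Assumed π | 12:12 | 16:8 |
|---|---|---|
| 0.3 SD | 29% | 26% |
| 0.5 SD | 65% | 60% |

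At 16:8, a shift of 0.3 SD is missed 74% of the time and moves the estimate by 0.3/3 = 0.10 SD. The estimate's own standard error with no period term is 1/√24 = 0.204 SD, so the displacement is 0.10/0.204, about half a standard error. At 0.5 SD it is 0.167/0.204, about 0.8.

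**Average behaviour.** The paired contrast was simulated with n = 24, simple randomization and 4,000 runs per setting. This is not the full daily model.

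| π | SD of estimate, no period term | SD with period term | Type I error, no period term |
|---|---|---|---|
| 0 | 0.20 | 0.21 | 4.8% |
| 0.5 SD | 0.23 | 0.21 | 4.8% |
| 1 SD | 0.29 | 0.21 | 4.5% |

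Mean bias was zero to simulation accuracy in every row. The 0.29 agrees with √((1 + 1)/24).

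**Which parameter is affected.** A shift that is constant over the 7 days, with complete days, moves the transfusion main effect. It therefore moves the between-visit contrasts and the 7-day mean comparison of aim 1. It does not move the transfusion-by-day interaction. That interaction is affected only if the day-by-day profile differs between periods, and then by the same fraction.

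**The case against.** **The primary test is an interaction with a visit-specific baseline.** This stands in large part. The fractions above are not biases of the tested interaction unless the 7-day profile changes with period, and the 3-day baseline removes at least part of any shift already present before the visit. It does not clear the contrasts or the aim 1 comparison. The baseline also removes only pre-existing shifts, and only as far as its fitted coefficient allows.

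**The missing period term may be in an analysis plan not shown.** Possible, and the general statement about accounting for the crossover could cover it. But the point does not rest on silence. The Randomization section states a condition that a period term would make unnecessary, and the model terms that are stated do not include one.

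**Stronger readings that the documents do not support.** A reader might infer that any time trend biases the result or inflates type I error. It does not: averaged over randomizations the bias is zero and the error rate stays near 5%. A reader might also infer that the planned group size fails. But the stated purpose is to estimate an SD, and a pooled two-group SD from 24 people has 22 df at any split, so 12 per group is not assured rather than missed. Finally, a chemotherapy main effect may seem necessary. It adds little to a within-person comparison in which a subject effect already absorbs between-person differences.

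**Simple randomization is a disclosed choice.** Correct. In an open-label trial where the coordinator who approaches patients also randomizes them, blocking within small strata has a real predictability cost.

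**Conclusion.** The point holds as a weakness in how the period effect is handled. The protocol makes the crossover's protection depend on an observation that about 24 people can seldom settle, and the stated model does not supply the protection directly. Conditional on the split, 25% (15:9) to 33% (16:8) of an unabsorbed period shift enters the between-visit contrasts and the 7-day mean comparison. Splits at least as uneven as these have probability 31% and 15% among 24 evaluable. With a 1 SD shift, leaving out the period term raises the SD of the estimate from about 0.21 to 0.29.

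These sizes rest on assumed shifts of 0.3 to 1 SD of the paired difference, on 24 complete pairs, and on a paired contrast rather than the full daily model. If sequences turn out equal, or no shift remains after baseline adjustment, the estimate is not displaced.

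The stratification has no effect at allocation, whatever the assumptions. The figure of 12 per group is a target with a 16% chance among exactly 24 evaluable and an 80% chance among 30 with no loss.

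**What to change.** 1. **Primary analysis.** Name period (first or second study visit) as a fixed effect in the primary model, and add period-by-day where the transfusion-by-day interaction is tested. Cost: 1 df for period, plus 1 for period-by-day if day is linear or 6 if the seven days are categories. In the paired simulation, the precision cost when no shift exists was an SD of 0.21 against 0.20.
2. **Randomization.** Delete the reliance on no period effect being observed, and say that the model adjusts for period whether or not one is seen. Investigators outside the Data Monitoring Committee have no accelerometer data until the trial ends, so this can still be prespecified credibly.
3. **Stratification.** State that simple randomization within the chemotherapy strata gives no balance, and either drop the stratification claim or make it work. The option is permuted blocks of varying size within strata for participants still to be randomized. The cost is a mid-trial change of allocation list and some predictability in an open-label trial. With the period term in place, this step is optional.
4. **Sample size.** Describe 12 per group as a target that the design does not assure. Blocking alone would not assure it either: if 24 of a 15:15 allocation are evaluable at random, the chance of 12:12 is C(15,12)²/C(30,24) = 34.9%.
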